## Abstract

**Background:**

Although physical inactivity has been linked with numerous chronic health conditions and overall mortality, the majority of English adults report doing insufficient physical activity. To increase population physical activity levels, researchers have called for more community-level interventions. To evaluate these complex public health interventions, innovative study designs are required. This study protocol describes *Devon Active Villages*, a community-level intervention providing physical activity opportunities to 128 rural villages in southwest England, and the methods used to evaluate its effectiveness in increasing physical activity levels.

**Methods/Design:**

A stepped wedge cluster randomised trial will be used to evaluate whether *Devon Active Villages* leads to increased physical activity levels in rural communities. Community engagement will help tailor activity programmes for each village; communities will then be supported for a further twelve months. The intervention will be delivered over four periods, each lasting twelve weeks. Data collection consists of a postal survey of a random sample of adults aged 18 years and over, at baseline and after each of the four intervention periods. The questionnaire includes questions on participant demographics, physical activity behaviour, local environment characteristics, awareness of local activity programmes, and psychosocial factors. Based on detecting an increase in the proportion of people who meet physical activity guidelines (from 25% to 30%), at least ten respondents are needed from each of the 128 villages at each stage (80% power at the 5% level of significance). Anticipating a 20% response rate, 6,400 questionnaires will be sent out at each stage (i.e., 50 surveys to each village). Using data from all five periods, a comparison of study outcomes between intervention and control arms will be performed, allowing for time period (as a fixed effect) and the random effect induced by correlation of outcomes (clustering) within villages.

**Discussion:**

This paper describes the use of a stepped wedge cluster randomised trial to evaluate a complex, community-level physical activity intervention in an under-studied population of adults in rural communities in southwest England. The study addresses gaps in the current literature by providing new insights into physical activity levels in this population.

**Trial Registration Number:**

Current Controlled Trials ISRCTN37321160

## Background

In developed and many developing countries physical inactivity is one of the most important public health problems of the 21^st^ century [1]. There is strong evidence linking physical inactivity with various chronic conditions, such as coronary heart disease, stroke, type 2 diabetes, cancer, obesity and mental health problems [1-3], and physical inactivity has been identified as a leading risk factor for mortality, estimated to cause 6% of deaths globally [4]. In contrast, the numerous benefits of a physically active lifestyle have been well documented [3]. Despite the preceding evidence, in England only 29% of women and 39% of men report doing sufficient physical activity to meet the minimum recommended guidelines of 150 minutes of moderate intensity physical activity per week or 75 minutes of vigorous intensity physical activity per week [5]. This level of physical inactivity is estimated to cost the United Kingdom National Health Service £0.9 billion per year [6].

Substantial health benefits can be achieved through relatively modest changes in activity behaviour among large segments of the population [7], and therefore physical activity interventions are now considered to be as important to population health as other high profile interventions, such as those lowering tobacco use or reducing blood pressure [2]. Although the health benefits of physical activity are now well-established, little is known about the effectiveness of interventions designed to improve population physical activity [8]. The majority of physical activity interventions have been delivered at the level of the individual, aimed at changing personal behaviour [9]. To change population prevalence, interventions need to be effective, but they also need to reach large numbers of people. Although some individual-level interventions are effective, their reach is limited when compared with community-level interventions. It is community-level interventions that have the potential to produce long-lasting benefits for the whole community, but evidence as to which type of community-wide interventions are most effective is currently weak [10].

A recent review of research examining the effectiveness of community-level interventions to promote physical activity reported that many studies used weak evaluation designs, such as uncontrolled, pre-post evaluations, and could not attribute any observed changes to the intervention [10]. One example of a community-level intervention evaluation that did include control communities—but was non-randomised—was the ‘Cycling Demonstration Towns’ programme in England [11], in which the intervention involved town-wide media campaigns, personalised travel planning, cycle training, repair services, and cycling infrastructure improvements. A controlled, repeated cross-sectional study examined the effect of the intervention in six towns between 2005 and 2008 using telephone surveys of quota samples of local residents [11]. The average annual percentage increase in the number of cyclists on the road was 4%. Net increases were also found in the proportions of residents who reported cycling for at least 30 minutes on 12 or more days per month (0.97% or 1.65%, depending on the choice of control areas) [11].

Reviews of physical activity correlates suggest that a combination of personal, social and environmental factors are associated with physical activity prevalence [12], but there are very few evaluations of the effects of changes to either social or built environments, and studies of the built environment are almost exclusively restricted to urban environments [10,13]. Both urban and rural dwellings report similarly low levels of physical activity in adults: on average, 9.5 days per month (95% CI: 9.3-9.6) of moderate-to-vigorous intensity physical activity for at least 30 minutes [5]. Although 20% of the population live in non-urban dwellings [5], rural populations are generally understudied [13,14]. Additionally, access to recreational facilities and other environmental supports for physical activity (e.g., neighbourhood ‘walkability’, convenient access to destinations, and perceived safety) have been shown to be related to physical activity participation [15], with people in rural areas being more likely to report lack of facilities as a barrier to physical activity [16].

Randomised controlled trials are considered the most powerful tool in research design for evaluating interventions, due to their rigorous study design and strict randomisation procedures [17]. Traditional randomised controlled trials, where individual participants are randomised, are not always reproducible in the real world and tend to focus on individuals rather than communities, raising doubts about whether a subsequent scaling up of individual interventions to larger populations would lead to changes in population prevalence [18]. It has been suggested that when evaluating interventions that are by necessity delivered to groups rather than individuals, cluster randomised trials, which randomise groups (e.g., communities, villages, towns) and measure outcomes on individual participants within those groups, are more appropriate [9,19].

Cluster randomised trials commonly use a parallel group design, in which the clusters are randomised to either the intervention or control arm of the study. For practical reasons it is often not possible to deliver an intervention to many clusters at the same time. In addition, it is often regarded as unethical to withhold an intervention from a proportion of participants if it is believed that the intervention will do more good than harm. In these circumstances, stepped wedge trial designs [20], where the intervention is delivered sequentially to all trial clusters over a number of time periods, is an alternative to the traditional parallel groups design. In a stepped wedge design, clusters effectively cross over from the control to the intervention group. The stage at which the clusters cross over is randomised. Outcomes are measured on the study participants in all clusters at every time period so that each cluster provides data points in both the control and intervention conditions [21]. Examples of stepped wedge investigations include the efficacy of Hepatitis B vaccinations [22], the effect of housing improvements on respiratory health symptoms [23], and different tuberculosis treatments on number of disease episodes [24].

The objective of this paper is to describe the protocol of a stepped wedge cluster randomised trial for evaluating the effectiveness of a community-level intervention to increase physical activity in rural villages in southwest England. The intervention will identify community needs and then provide resources and support to initiate local activity programmes, ultimately aiming for the activities to become self-sustaining over time. The intervention is expected to improve physical activity participation after each village receives the intervention. It is also anticipated that changes will be observed in levels of social support, physical activity intentions, awareness and use of local facilities, and perceived village supportiveness of physical activity.

## Methods/Design

### Study design

The *Devon Active Villages Evaluation* (DAVE) protocol is based on a stepped wedge cluster randomised controlled trial design (Figure 1). During the DAVE study, the intervention will be rolled out sequentially to 128 rural villages (clusters) over four time periods. The evaluation will consist of data collection at five fixed time points (baseline and following each of the four intervention periods). The period in which the villages first receive the intervention will be randomly assigned, stratified by the seven regions of the county of Devon (see below). The intervention will be fully implemented by the end of the trial, with all 128 villages receiving the intervention: 22 first receiving the intervention at period 2, 36 at period 3, 35 at period 4, and 35 at period 5.

**Figure 1 F1:**
[figure not shown]
**Design of the DAVE study.** One cluster (C1, C2, C3 or C4) represents one group of intervention villages. Each time period (T1, T2, T3, T4, or T5) represents a data collection point. Each unit (control or intervention) represents one time period of one cluster.

### Setting and participants

*Devon Active Villages* is a community-level intervention coordinated by *Active Devon,* the Devon county partnership for sport and physical activity. Active Devon received circa £950,000 funding for the Devon Active Villages intervention from Sport England (the government body for sports promotion) and Devon County Council as part of Sport England’s ‘Rural Communities’ funding scheme. The Devon Active Villages Evaluation (DAVE) research study is being conducted by the University of Exeter in close liaison with Active Devon.

Devon is characterised by ten distinct regions, of which three are urban (Exeter, Plymouth and Torbay), and seven are rural (East Devon, Mid Devon, North Devon, South Hams, Teignbridge, Torridge and West Devon). All intervention villages are located in one of the seven rural regions. The Devon Active Villages intervention will provide activities for all age groups.

In the initial planning of the intervention, Active Devon identified 155 rural villages to receive the Devon Active Villages intervention across the course of three years. Prior to the intervention, Active Devon ran a pilot intervention with 15 villages, the outcome of which was used to inform the main intervention protocol.

### Recruitment and randomisation

Of the remaining 140 villages that were not part of the pilot, twelve could not be included in the evaluation due to engagement with local community members before baseline data collection had commenced. Thus, the remaining 128 villages (clusters) were recruited and randomised to first receive the intervention in one of the four periods, stratified by region. Villages with populations of 500–2000 people formed the sampling frame for the intervention. These population boundaries were set so that villages were large enough to have local facilities suitable for physical activity, but limited in the amount of activity opportunities they offered.

Data collection for the evaluation study will focus on adults aged 18 years and over. The study will use a repeated cross-sectional design, in which a random sample of people within each cluster will be surveyed at each stage. A complete list of all households in each of the 128 study villages will be obtained using the Postcode Address File (Address List Utility, Arc en Ciel, Version 3.1 PAF Quarter 1, 2011). The order in which households are approached to participate in the survey at each stage will be randomly generated. One adult per household will be randomly selected. If there are multiple eligible adults in the household, an invitation to complete the survey will be given to the adult who has most recently had a birthday.

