### Data collection

Postal questionnaires and participant information sheets will be sent out to participants at baseline (in the month prior to the first intervention period commencing) and within a week of each of the four intervention periods ending (Figure 2). The participant information sheet makes clear the voluntary nature of the study and therefore informed consent to participate in the study will be implied when participants return a completed questionnaire. If the number of completed questionnaires returned within three weeks of the initial mailing is insufficient, additional questionnaires will be sent out to new households. Participants will receive the questionnaire, a participant information sheet and a prepaid return envelope. It is possible that some individuals may receive the questionnaire on two or more occasions. In such cases, if returned, demographic variables (gender, age, height, weight) will be used to identify this wherever possible. These participants will remain in the analysis, but it will be recorded that each participant has completed the questionnaire on more than one occasion.

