#### Physical activity campaigns/programmes

The survey will contain questions on participants’ awareness of and participation in local physical activity campaigns. The survey will also ask about awareness of Devon Active Villages, participation in programme events, and opinions on the programme.

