### Sample size

To detect an increase from 25% to 30% in the percentage of people who meet guidelines for recommended physical activity levels, 10 participants need to be recruited from each of the 128 villages at each study period to achieve 80% power at the 5% significance level [30]. A recent pilot for a population study of travel behaviour in the United Kingdom achieved a response rate of 20% for a short questionnaire postal survey [31]. On this basis, 50 surveys will be sent out to each village at each stage, anticipating that we will obtain at least 10 responses per village per stage (20% response rate). This means that 6,400 surveys will be sent out at every stage with the expectation that at least 1,280 will be completed and returned. If this response rate is not achieved within three weeks of the surveys being posted, an additional five surveys will be sent out to extra households for every one survey missing (20% response rate).

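### No stated rule keeps already-mailed households out of later survey draws, so repeat mailings that name the programme can raise awareness in control villages at stages 2 to 4

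*Protocol article*

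**What the plan says.** The Recruitment and randomisation section describes the survey as follows: "The study will use a repeated cross-sectional design, in which a random sample of people within each cluster will be surveyed at each stage". It takes a complete household list for each village and adds: "The order in which households are approached to participate in the survey at each stage will be randomly generated". Within a household, "One adult per household will be randomly selected", by the last-birthday rule. On village size it says: "Villages with populations of 500–2000 people formed the sampling frame for the intervention". The Sample size section states that "50 surveys will be sent out to each village at each stage", with five further mailings for each return that is short of target.

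The Data collection section concedes: "It is possible that some individuals may receive the questionnaire on two or more occasions". Such people stay in the analysis and are flagged; "demographic variables (gender, age, height, weight) will be used to identify this wherever possible". New or extra households are mentioned only for top-ups within a stage. No passage removes households mailed at an earlier stage from a later draw.

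On content, the section on physical activity campaigns and programmes says: "The survey will also ask about awareness of Devon Active Villages, participation in programme events, and opinions on the programme". Awareness of the programme is listed as a secondary outcome under Outcome measurement.

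**The concern.** The article presents repeat receipt as something that may happen to some individuals. Five rounds of 50 mailings into villages of 500 to 2,000 people make it routine if each round is a fresh draw.

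The consequence falls on the awareness outcome. A household in a village still in control mode that was mailed earlier has been asked about the programme by name, so a later respondent there can report awareness that the survey created. Control-mode awareness rises and the contrast between modes shrinks. The plan already treats early exposure as a problem: twelve villages were left out of the evaluation because local people had been engaged before baseline.

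The planned flag does not capture this. Matching on demographics can identify only people who returned two questionnaires. At an expected 20% response, most households already mailed will never have returned one.

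**Working it through.** **Plan's own mailing figures.** 128 × 50 = 6,400 sent, 128 × 10 = 1,280 returned, and 10 / 0.20 = 50 per village. These reproduce.

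**Inputs.** From the article: 50 mailings per village per stage, five stages, 500 to 2,000 people per village, and 22/36/35/35 villages crossing over at periods 2/3/4/5. Assumed, because the article does not give them: household size 2.3 (range 2.0 to 2.5), and village sizes uniform over 500 to 2,000 where an average is needed.

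**Control villages by stage.** 128 at stage 1, then 128 − 22 = 106, 106 − 36 = 70, 70 − 35 = 35, and 35 − 35 = 0 at stage 5. Contamination of control mode can therefore occur only at stages 2 to 4.

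**Overlap if orders are independent.** With H = population / 2.3 households, the expected share of stage k mailings going to an already-mailed household is 1 − (1 − 50/H)^(k−1), before top-ups.

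| Population | H | Stage 2 | Stage 3 | Stage 4 |
|---|---|---|---|---|
| 500 | 217 | 23.0% | 40.7% | 54.3% |
| 1,000 | 435 | 11.5% | 21.7% | 30.7% |
| 2,000 | 870 | 5.7% | 11.2% | 16.3% |
| Uniform 500 to 2,000 | – | 10.6% | 19.9% | 28.1% |

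**Control-mode average after baseline.** (106 × 10.6 + 70 × 19.9 + 35 × 28.1) / (106 + 70 + 35) = 3,500 / 211 = 16.6%, about 17%. The same sum gives 14.6% at 2.0 people per household and 18.0% at 2.5.

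**What matching could find.** If response is unrelated to earlier response, the share of stage 4 mailings going to a household that has already returned a questionnaire is 1 − (1 − 10/H)^3. That is about 13% at H = 217 and 3% at H = 870, against 54% and 16% already mailed.

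**Why period adjustment does not repair it.** Suppose a fraction q of otherwise unaware people become aware through an earlier mailing, equally in both modes. Awareness p becomes p + q(1 − p), and the risk difference becomes (1 − q) times its true value. As an illustration only, assume true awareness of 5% and 20%, and that 30% of re-mailed people recall the name, so q = 0.17 × 0.30 ≈ 0.05. Awareness becomes 9.75% and 24%. The difference falls from 15 to 14.25 points, and the odds ratio from 4.75 to about 2.9. The odds ratio, which the planned logistic model would report for a binary outcome, suffers more because control awareness starts low.

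**Feasibility of non-overlapping samples.** Stages 1 to 4 need 4 × 50 = 200 addresses. A village of 500 has 200 households even at 2.5 per household. All five stages need 250 addresses, or 250 × 2.3 = 575 people. With the top-up rule, mailings per stage are 50 + 5(10 − 50r) at response r:
- r = 0.15: 62.5 per stage, 312.5 over five stages, about 719 people. Stages 1 to 4 alone need 250 addresses, about 575 people.
- r = 0.10: 75 per stage, 375 over five stages, about 863 people. Stages 1 to 4 alone need 300 addresses, about 690 people.

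**The case against.** Several counter-arguments have force.

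- **The reading is an inference.** The article does not literally say that the draws are independent or that earlier households stay eligible, and a full protocol might settle it. That stands as a caveat. Independent drawing is still the natural reading: an order is generated for each stage, no exclusion is stated, and repeat receipt is expected.
- **The shares are ceilings.** They count envelopes sent to households. A questionnaire may go unread, and the last-birthday rule may pick another adult. This stands.
- **Stage 5 is tempting but irrelevant here.** A reader might cite the largest overlaps, about 65%, 39% and 21% at stage 5 for 500, 1,000 and 2,000 people, as contamination of controls. All villages are in intervention mode by then, so the documents do not support that use.
- **The primary outcome.** A reader might infer bias in the proportion sufficiently active. Expected overlap at a given stage is the same in both modes and period is adjusted for, so a common prompting effect is absorbed. Only an interaction between earlier mailing and the intervention would remain, and nothing in the article shows one.
- **Other routes to awareness.** The twelve-week engagement phase before delivery can also inform residents in control mode, and changing the mailing would not remove that.
- **Precision.** Village-level robust standard errors cover correlation between repeat responders for binary outcomes. The point does not rest on precision.
- **The remedy is not free everywhere.** At 500 people and 2.3 per household, 217 − 200 = 17 fresh addresses remain at stage 5, so 33 of 50 mailings (66%) would still be repeats, no better than independent drawing. This is correct, but it concerns the stage without controls.

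**Conclusion.** The point holds as an avoidable weakness in the sampling scheme that mainly affects one secondary outcome. If the household orders are independent, about 17% of post-baseline control-mode mailings go to households already sent a questionnaire naming the programme. By stage 4 the share ranges from about 16% in the largest villages to 54% in the smallest. These figures rest on an assumed 2.3 people per household, the average also on uniform village sizes, and all exclude top-ups, which would raise them. They are upper limits on actual exposure.

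The likely effect is dilution of the awareness contrast, towards no difference. Its true size cannot be derived from the article, because neither baseline awareness nor recall is given. The article's wording understates how often repeats would occur, and the planned matching would miss most prior exposure.

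**What to change.** Generate one random address order per village at the start and work down it across all five stages, top-ups included. Return to earlier-mailed addresses only when the list is exhausted. Each successive block is still a random sample of the village's households. Keep the record of mailed addresses, so that earlier mailing is known from the list, and retain the planned demographic matching to identify individuals who respond twice.

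The number of mailings does not change. Before top-ups, overlap disappears at stages 1 to 4 in any village with at least 200 households. It remains at stage 5 below 250 households, and in larger villages if response is low. A number printed on the questionnaire would tie each return to an address, but it is optional. It would have to be disclosed in the information sheet, may need ethics review, and identifies a household, not a person.
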